## Blinding/unblinding

Everyone involved in the study will be blinded to the study arm allocation of each participant, except for the study nurses administering the vaccine.

When the primary outcome of the study has been reached (28 days after the second dose), an interim analysis will be conducted to determine whether the reduced vaccine dose induces an inferior immune response as compared to the regular dose or not. In case of non-inferiority, there will be no need for unblinding before the end of the trial. In case of inferiority, study participants will be unblinded, informed about which study arm they were allocated to and offered a third dose (of 30µg) of BNT162b2.

## Study flow

### Participant information and consent procedure

A research nurse checks the study eligibility criteria and informs the candidates on the possibility to participate in the study. Participant information and consent includes explaining that the national number will be recorded on site by the investigator for possible later data linkage. The participant information and consent will also include that a trusted third party (TTP) will receive and use the national number to link with administrative data. This data linkage is planned to obtain a more complete data set that will be used for the analysis of possible hospitalization and other medical activities billed to the health insurance.

Participant information and consent includes explaining that the email and mobile number from study participants will be recorded in a separate and protected form in the database hosted by the

occupational physician. These data are only used to send emails and text messages to the participant for this study.

After having had the possibility to think and discuss about their participation, the participant gives written informed consent and provides the research nurse with their email address and telephone number that they intend to use the next 12 months.

### **Baseline activities**

After the participant has given written informed consent, the research nurse completes the Subject ID log with participant's name, national number and study number. The participant national number is collected and kept on site by the research nurse in the Subject ID log. Each of the participating sites will transfer this local Subject ID log at study closure to the TTP for data linkage, following the procedure detailed in the authorization of the Information Security Committee.

The research nurse creates a new participant in the study eCRF (hosted on LimeSurvey) and enters the date of consent, gender, year of birth, height, weight. They will also register whether the participant has had a past SARS-CoV-2 infection (i.e. positive nasopharyngeal swab, positive serology test).

Once the information is entered by the research nurse in the eCRF, the participant automatically receives an email (subject "Clinical Trial Message" and starting with "Dear Madam, Dear Sir") with a link to the data entry screens for the patient-reported-outcomes (PROMs). In order to have a second identity check, the participant first enters year of birth and their study number.

The research nurse can view the PROMs of his/her subjects and only exceptionally make corrections upon explicit request by the participant. Each such change will be logged and needs a justification. At all times the research nurse can indicate in the system the early end of study (and stop sending emails to the participant to complete the PROMs), e.g. in case of withdrawal of consent, if known to the research nurse. In case of withdrawal of consent, data already collected will be kept in the study data.

### **Vaccination**

Depending on the randomization, participants will either receive two doses of 20µg or two doses of 30µg of the BioNTech/Pfizer SARS-CoV-2 mRNA vaccine, with a three week interval between both doses.

### **Sampling visits**

An overview of the different sample types and volumes at each study visit is summarized in table 1. Venous blood will be collected on the day of the first and second dose as well as four weeks after the second dose, and six months and one year after the first dose. Five mL of blood will be collected from all study participants at all study visits. From a random selection of 20 participants per study arm (40 in total), 36mL of heparinized blood will be collected on the day of the first dose as well as four weeks after the second dose and six months after the first dose.

The sampling activity (date, sample types collected) is documented in the eCRF. Samples are handled as detailed in the sampling manual.

One week after each vaccination dose, participants will be invited by email and text message by the research nurse to fill in a questionnaire collecting information on the reactogenicity of the vaccine.

### **Monitoring of adverse reactions**

Suspected unexpected serious adverse reactions, serious adverse reactions, and adverse reactions with grade equal or more than 3 will be monitored for the duration of the study period. The study nurse will complete the reporting form (annex 4) and forward this to the study coordinator, who in turn will report this immediately to the Belgian Federal Agency for Medicines and Health Products.

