### 3.2. SECONDARY OBJECTIVES AND OUTCOMES

- GMT of RBD-specific binding antibodies at the time of the second dose, six months and one year after the first dose.
- GMT of neutralizing antibody titers against wild type and variant SARS-CoV-2 viruses at four weeks after second dose administration.
- Cellular immunity parameters (i.e. Memory B-cell responses, T-cell responses, etc) at all clinically and biologically relevant time points.
- Safety and reactogenicity of the different vaccine regimens as defined by the severity, duration and amount of adverse events experienced after each vaccine dose.

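### The safety outcome is adverse events, but staff-reported monitoring takes only adverse reactions, and neither the assessor of relatedness nor that person's blinding is stated

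*Protocol*

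**What the plan says.** Section 3.2 lists safety and reactogenicity as a secondary outcome, measured by the "severity, duration and amount of adverse events experienced after each vaccine dose". Nothing there restricts the outcome to events thought to be caused by the vaccine.

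The section on monitoring of adverse reactions names three categories: suspected unexpected serious adverse reactions, and then "serious adverse reactions, and adverse reactions with grade equal or more than 3 will be monitored for the duration of the study period". On who does this, it says: "The study nurse will complete the reporting form (annex 4) and forward this to the study coordinator". The coordinator reports onward to the medicines agency. Section 8.4 lists Appendix 4 as the SUSAR form; its content is not shown. No person is named as the assessor of relatedness.

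The section on blinding reads: "Everyone involved in the study will be blinded to the study arm allocation of each participant, except for the study nurses administering the vaccine".

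Participants also report for themselves. Under sampling visits: "One week after each vaccination dose, participants will be invited by email and text message by the research nurse to fill in a questionnaire" on reactogenicity. The section on epidemiological data adds participant questionnaires at the Table 1 time points, covering reactogenicity and how severe adverse events were. Table 1 places questionnaires on the day of dose 1, at 6 months and at 1 year. It does not show the one-week questionnaires.

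Finally, the consent procedure and section 5.2 plan a linkage to health-insurance data on hospitalization and billed care, to start only once the Information Security Committee has approved it.

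**The concern.** The outcome is defined on *events* and the staff-reported collection on *reactions*. The difference is a judgement of relatedness, made before anything is written down.

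A randomized comparison does not need that judgement case by case, because the 30 µg arm shows what occurs at the reference dose. If relatedness decides what is recorded, the counts in the two arms reflect attribution as well as occurrence. If the person attributing knows the dose, attribution can differ between arms. Section 7.2 expects fewer and milder side effects at the lower dose, so an unblinded reporter would start from a stated expectation.

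This belongs in the protocol. A statistical analysis plan can choose how to tabulate events, but it cannot recover events that the collection rule left out.

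**Working it through.** The Protocol gives no safety event rate, hypothesis or power, so there is no figure to reproduce. The check sets the sources of safety data side by side.

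| Source | Who reports | What it takes in | Causality condition | When |
|---|---|---|---|---|
| Outcome (3.2) | – | Adverse events: severity, duration, amount | None | After each dose |
| Monitoring of adverse reactions | Study nurse, by form | SUSARs, serious reactions, grade 3 or higher reactions | Yes, in all three | Whole study |
| Sampling visits | Participant | Reactogenicity | None stated | One week after each dose |
| Epidemiological data, Table 1 | Participant | Reactogenicity, severity of adverse events | None stated | Table 1: dose 1, 6 months, 1 year |
| Consent procedure, 5.2 | Linked insurance data | Hospitalization, billed care | None | After approval |

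**Step 1: which events lack a staff route.** The second row is the only staff-reported one. A reaction is an event suspected to be caused by the product, so all three categories pass through a relatedness filter. A serious or grade 3 or higher event judged unrelated falls in none of them.

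**Step 2: whether the other sources close the gap.**
- *Timing.* Doses are three weeks apart, so the second one-week questionnaire falls at about week 3 + 1 = 4. The next one in Table 1 is at 6 months, about week 26, which is 26 − 4 = 22 weeks later. The last is at 1 year, 52 − 26 = 26 weeks after that. Late events do have a participant-reported route, but by recall over long intervals. The questionnaire (Appendix 2) is not shown, so its recall period and content cannot be checked.
- *Loss.* Under the discontinuation criteria, participants who do not supply questionnaire information leave the study, so this source can fail for a participant who does not respond.
- *Linkage.* Section 5.2 describes it as possible and later, conditional on approval and based on sickness-fund financial data. The subject logs go to the third party at study closure. Nothing stated says it would yield an event grade.

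**Step 3: who judges relatedness, and whether blinded.** The study nurse completes the form and the coordinator receives it. The blinding section exempts vaccinating nurses only, so the coordinator is blinded. Whether the nurse who completes the form also vaccinates is not stated. The Protocol therefore permits an unblinded reporter without establishing one, and it requires no blinded assessor.

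**The case against.** The strongest reply is that the monitoring section describes expedited reporting. It uses a SUSAR form and ends at the regulator, and nothing says that these reports are the data set for comparing the arms. On this view the outcome in section 3.2 is answered by the one-week questionnaires, completed by blinded participants with no staff causality filter stated. Much of this stands: the early reactogenicity comparison does not rest on staff attribution. It does not remove the gap, because no other staff-reported route is given for serious or severe events, and safety is an objective alongside reactogenicity.

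Three stronger readings are tempting, and the documents do not support them:

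- *Unrelated events, or events after the first weeks, are never recorded.* The 6-month and 1-year questionnaires ask about adverse events, a linkage is planned, and the monitoring section captures related serious and severe events throughout the study.
- *An unblinded role makes the causality judgement.* No assessor is named, completing a form is not judging causality, and the reporting nurse is not said to be one who vaccinated.
- *The whole safety comparison depends on that judgement.* The participant-reported data do not pass through it.

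It is also fair that Appendix 4 is not shown and may already hold a relationship or assessor field. Such a field would not widen the categories that the text says are monitored.

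**Conclusion.** The point holds in a limited form. The safety outcome is adverse events, and the only staff-reported, study-long collection is restricted to adverse reactions. Serious or grade 3 or higher events judged unrelated therefore reach the data only through participant questionnaires or a conditional linkage. The assessor of relatedness and that person's blinding are unspecified, while the form starts with a role that may be unblinded.

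The size cannot be calculated. It is the number of serious or grade 3 or higher events judged unrelated, and the Protocol gives no rate for these. For serious events it expects very few or none, so in 150 participants the numbers affected are probably small. No bias between the arms is shown, only an avoidable opening for one.

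The conclusion rests on reading *reaction* in its usual sense of an event with suspected causality, and on the main text alone, since Appendices 2 and 4 are not shown. The change is worth making because it is cheap and an omitted event cannot be restored at analysis.

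**What to change.** 1. In the section on monitoring of adverse reactions, record all serious adverse events and all grade 3 or higher adverse events for the whole study, whatever their judged relationship to the vaccine.
2. Make relationship a field on the form, completed by an investigator who is already blinded under the blinding section, and name that role.
3. Compare the arms on all recorded events, with related events as a subset.
4. Leave expedited reporting of suspected reactions as written.
5. Reconcile section 3.2 with the sections on blinding, sampling visits, monitoring of adverse reactions and epidemiological data, and with Table 1. In particular, add the one-week questionnaires to Table 1 and state whether the nurse who completes the form may be one who vaccinates.

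The cost is a small number of additional reports, given the few serious events expected, and possibly one field on the existing form. No extra visit or sample is needed.

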### **End of the trial**

The trial will end when the last study participant has been sampled one year after first dose administration.

## 4.1. DATA MANAGMENT

### Safety

Based on previously published phase 2 and 3 data of both vaccines that will be used in this study, very few to no serious adverse events are expected (6,8). Besides vaccination, no safety issues linked with the other study procedures are expected either. As a consequence this is considered a low risk study.

### Data collection

Laboratory data (samples) and epidemiological data (questionnaire) will be collected as described above. Each participant will receive a unique identifier code at the start of the study that will be used both on the samples and the questionnaires through the whole study period.

#### Laboratory data

Blood samples will be collected as indicated in table 1. Serum will be isolated from serum gel blood collection tubes and will be used for:

- SARS-CoV-2 specific binding antibody quantification: using an *in-house* anti-RBD IgG ELISA.
- Neutralizing antibody capacity measurement against the wild type Wuhan strain and at least one variant of concern: using a virus neutralization assay.

Peripheral Blood Mononuclear Cells (PBMC) will be isolated from heparinized blood on the day of blood draw and will be stored in liquid nitrogen for further analyses. These include:

- Memory B-cell responses: using B-cell ELISpot of flow cytometry
- T-cell responses: using intra-cellular cytokine staining

Samples will be collected at the research sites by a research nurse of Mensura EDPB.

#### Epidemiological data

Socio-demographic characteristics and SARS-CoV-2 initial status (date of last PCR test) will be collected by the research nurse at the time of inclusion and will be pseudonymized (without the identity of the participant but with a unique participant code, see further) transferred to Sciensano after informed consent of the participant was obtained. Additional questionnaires will be filled in by the participants given time points (see Table 1), and will provide information on reactogenicity and severity of the adverse events. All questionnaires will be completed through a secured online application (see further).

### Data flow and management

Blood collection tubes as well as labelling stickers will be provided by Sciensano. For the entirety of the study, material will be provided in batch and a transport will be organized between Sciensano and the research sites. After collection, samples will be handled following the appropriate SOP.

Epidemiological and laboratory data will be linked via a unique code assigned to each participant. This code will start with the first letters of the research site location followed by a three digit number (e.g. "BRU\_001" for the first participant, "BRU\_002" for the second one, and so forth).

A sticker labelled with this code will be affixed by the research nurse on each tube at the time of sampling, and the same corresponding code will be entered in each questionnaire, enabling the link for data analysis. For the planned days, the labels will also include an identifier of this point (e.g. "D00", "D28" etc). This unique code must stay the same during all the duration of follow-up and a list of all participants and their assigned codes will be kept in a secure and protected way by the occupational physician.

Questionnaires are filled in online through LimeSurvey. Before sampling takes place, an email will be sent to the participant containing a questionnaire link and the unique participant code. It will take around

five minutes for the participant to fill in the questionnaire. If the questionnaire is not filled in yet at the moment of sampling, it will be filled in together with the research nurse. A confirmation email will be sent to the research nurse when a questionnaire is correctly received. LimeSurvey is a web application running on a server located within Sciensano's datacenter. The application and its associated database are located on the same server. It means there are no data located outside Sciensano. Access to the administration of the LimeSurvey application is restricted to a limited number of people involved in the administrative management of the survey, who are authenticated with a username and password. All files will be kept on the Sciensano SQL server with restricted access.

Login to the shared server is password controlled. Each user/investigator or research nurse will receive a personal login name and password and will have a specific role which has predefined restrictions on what is allowed on the server. Furthermore, users will only be able to see data of subjects of their own site. Any activity in the software is traced and transparent via log files.

Direct access to all study records, including source documents and the eCRF will be granted to authorized representatives from the Sponsor, host institution and the regulatory authorities to permit study-related monitoring, audits and inspections. The Data Manager will review the eCRFs to make certain that all items have been completed. Incorrect or inappropriate entries in the eCRFs will be returned to the research nurse for correction (data queries), if not already captured using automated data entry checks. Subject privacy must be respected at all times, in accordance to GDPR, GCP and all other applicable local regulations. The investigator/study team should immediately notify the sponsor if he or she has been contacted by a regulatory agency concerning an upcoming inspection.

The data capture software analysis, development and testing will be performed according to the procedures of the Sponsor. Quality check of data management and data entry will be performed in accordance with the standard operating procedures of the Sponsor.

## Analysis

### Data analysis

Analysis of all data collected within this study will be performed by Sciensano. Questionnaire responses will always be coded. All analyses will be performed in R (R Core Team (2018), available from <https://www.R-project.org/>), STATA or SAS.

Meaningful laboratory results of each participant will be communicated to the research nurse who will be able to communicate them to the participants. This includes the anti-SARS-CoV-2 antibody status at the primary endpoint and at the end of the study.

As already mentioned, these tests are for research and not diagnostic purposes, and depending on lab capacity, there will be a delay in the communication of the results. The global results of the study will be communicated to each participating center at the end of the study in the form of a report and/or presentations.

### Statistical analyses

The analysis described here will be coordinated by the Sponsor. Any later analyses on the linked data will also be conducted by the Sponsor.

All of the participants who meet the eligibility criteria will be included in the main analysis. Descriptive analyses will be used to report participant characteristics. The level of antibody titers in each of the study arms will be analyzed with the Kruskal-Wallis test, while participant demographics (e.g. age, gender) will be taken into account (confounders). Furthermore, risk factors and correlations with antibody detectability will be evaluated. P-values below 0.05 will be considered statistically significant.

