## 3. Objectives and outcomes

We aim to include 150 adults aged 18-55 years from five Mensura EDPB sites. These will be equally randomized in two study arms receiving two doses of:

- Arm 1: 20µg BNT162b2
- Arm 2: 30µg BNT162b2

We aim to include up to 25 previously SARS-CoV-2 infected subjects per arm. The objectives of this study include assessing the immunogenicity (both humoral and cellular), safety and reactogenicity of a reduced vaccine dose.

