## Sample size

The primary analysis is a non-inferiority comparison at 28 days after the second dose, for the GMT of antibodies binding to the RBD of SARS-CoV-2, comparing the reference dose (30µg BNT162b2) with the reduced dose (20µg BNT162b2).

Currently available data from published and ongoing COVID-19 vaccination trials indicate that:

- RBD-specific antibody titers (GMT, arbitrary units) 28 days after the second dose of BNT162b2 equals 2125. The standard deviation on the log scale (base 10) is 0.27 (PICOV-VAC trial).

The following assumptions are made in the sample size calculations:

- The non-inferiority margin is -0.15 absolute difference of GMT on log scale (base 10), between a reduced dose and regular dose vaccine schedule.
- The standard deviation of GMT on the log10 scale is 0.27 for BNT162b2, based on the currently available data.
- The true difference of GMT on log10 scale is 0.
- A two-sided 2.5% family-wise error rate (at cohort level).

Based on these assumptions, the comparison between both doses will need a minimum of 50 participants (infection naïve) per group to achieve 90% power. In order to be able to better evaluate reactogenicity however, we aim for a larger sample size.

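### The primary comparison is sized on infection-naïve participants but the main analysis includes everyone eligible; if the dose effect is smaller after infection, pooling can hide a deficit in the naïve

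*Protocol*

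**What the plan says.** The Sample size section of the protocol states that "the comparison between both doses will need a minimum of 50 participants (infection naïve) per group to achieve 90% power". Statistical analyses then defines the main analysis differently: "All of the participants who meet the eligibility criteria will be included in the main analysis".

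Eligibility does not separate the two groups. The inclusion criteria are employment and age; the exclusion criteria are earlier COVID-19 vaccination and pregnancy or breastfeeding. Section 3 expects infected participants: "We aim to include up to 25 previously SARS-CoV-2 infected subjects per arm". With 150 participants randomised equally, that is up to 25 of 75 per arm, or one third.

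Trial randomization allocates without regard to infection status and stratifies by age and gender only. Statistical analyses names demographics as the factors to take into account and does not mention past infection. Section 3.1 states the primary objective without limiting it to naïve people.

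**The concern.** The sample size and the main analysis refer to different populations, and the protocol does not say which one the non-inferiority claim is about. In a non-inferiority trial, anything that shrinks a true difference works in favour of the claim. If prior infection makes the response less sensitive to dose, one third of each arm contributes little information about the dose effect, and a deficit in naïve recipients looks smaller than it is. The same result decides whether participants are unblinded and offered a further dose (Discontinuation criteria; Blinding/unblinding), so the choice of population has consequences beyond the report.

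A second effect acts on precision. If infected and naïve participants differ in mean titre and infection status is not adjusted for, the pooled spread exceeds the planning SD and power falls.

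**Working it through.** **Inputs from the protocol.** Margin 0.15 log10, SD 0.27, true difference 0, two-sided 2.5% error, i.e. one-sided 1.25% (Sample size); 75 per arm, up to 25 of them infected (section 3). One-sided 2.5% is shown alongside.

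**Assumptions.** f is the dose effect in infected participants as a share of that in naïve participants. m is the log10 difference in mean titre, infected minus naïve. The protocol gives neither, so both are varied. The calculation compares mean log10 titres by normal approximation, with an SD of 0.27 within each infection group and 25 infected in each arm.

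**1. The plan's own figure.** n per group = 2 × 0.27² × (z₁₋α + z₁₋β)² / 0.15² = 6.48 × (z₁₋α + z₁₋β)².
- One-sided 1.25%, 90% power: 6.48 × (2.241 + 1.282)² = 80.4, so 81.
- One-sided 2.5%, 90% power: 6.48 × (1.960 + 1.282)² = 68.1, so 69.
- One-sided 5%, 90% power: 56.
- One-sided 2.5%, 80% power: 51.

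The stated 50 for 90% power is not reproduced. With 50 per group, SE = 0.27 × √(2/50) = 0.054 and 0.15/0.054 = 2.778. Power is Φ(2.778 − 2.241) = 70.4% at one-sided 1.25%, or Φ(2.778 − 1.960) = 79.3% at one-sided 2.5%.

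**2. Dilution.** For a naïve deficit d, the pooled deficit is (2/3)d + (1/3)f·d. The pooled variance is 0.27² + (1/3)(2/3)m², and SE = SD × √(2/75). The chance of declaring non-inferiority is Φ((0.15 − pooled deficit)/SE − z₁₋α).

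With d = 0.15, f = 0 and m = 0, the pooled deficit is 0.10 (GMT ratio 0.79 instead of 0.71) and SE = 0.0441. The chance is Φ(1.134 − 2.241) = 13.4%, or Φ(1.134 − 1.960) = 20.4%.

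| f | m | Pooled deficit | One-sided 1.25% | One-sided 2.5% |
|---|---|---|---|---|
| 0 | 0 | 0.100 | 13.4% | 20.4% |
| 0 | 0.6 | 0.100 | 7.2% | 12.0% |
| 0.5 | 0 | 0.125 | 4.7% | 8.2% |
| 0.5 | 0.6 | 0.125 | 3.2% | 5.8% |
| 1 | 0 to 0.6 | 0.150 | 1.25% | 2.5% |

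With f = 0, the pooled test returns to its nominal level only when (2/3)d = 0.15, that is d = 0.225, a GMT ratio of 0.60 in naïve participants.

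**3. Power at a true difference of 0, 75 per arm, unadjusted.**

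| m | Pooled SD | One-sided 1.25% | One-sided 2.5% |
|---|---|---|---|
| 0 | 0.270 | 88% | 93% |
| 0.3 | 0.305 | 78% | 85% |
| 0.5 | 0.358 | 63% | 73% |

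**4. Adjustment alone.** Adjusting for infection status removes m from the variance but leaves the weights at 2/3 and 1/3. The result is then the m = 0 row for each f. Adjustment recovers power but does not undo dilution.

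**The case against.** The strongest reply is that the naïve comparison was intended all along. 75 − 25 leaves exactly the 50 naïve participants per arm in Sample size, that section sets the error rate at cohort level (a term it does not define), and Statistical analyses speaks of the main rather than the primary analysis. Conversely, section 3.1 does not restrict the objective, and for a mixed target population the pooled difference is not biased. Both readings are fair. Both also mean that one of the two sections has to change, and an unseen SAP could not settle this without departing from a sentence in the protocol.

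A reader might infer that pooling is shown to bias the trial towards non-inferiority. It is not. Dilution requires f below 1, and the protocol reports no titres or dose effect for infected people. Section 2 only mentions a single-dose schedule for the previously infected as a strategy already in use, which makes a smaller dose effect plausible and no more. The largest figures also need the full 25 infected per arm, no dose effect in them, and a naïve deficit exactly at the margin. Moreover, a titre shift without adjustment makes non-inferiority harder to declare, so the two effects pull in opposite directions.

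Three further inferences lack support:
- That the SD of 0.27 excludes infected participants: the infection mix of its source is not given.
- That naïve status rests on recall: Baseline activities counts earlier positive serology, and serum is drawn from everyone on the day of dose 1.
- That missed or wrong second doses would pull the result towards no difference: the protocol does not address them, they could act either way, and such analysis sets are usual SAP content.

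**Conclusion.** The point holds as a mismatch between the population used for sizing and the population analysed, with a conditional consequence. The mismatch is in the protocol's own text and needs no assumption. The inflated chance of a non-inferiority verdict is measured against the naïve comparison and rests on the assumed f and m; it ranges from nominal at f = 1 up to 13.4% (one-sided 1.25%) or 20.4% (one-sided 2.5%) at f = 0. The loss of power depends only on a titre shift that is not adjusted for. All figures assume a comparison of mean log10 titres; the Kruskal-Wallis test named in Statistical analyses does not test the margin, which is a separate matter. The point deserves correction before any unblinded analysis because the choice of population can change the primary conclusion.

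**What to change.** State in Statistical analyses that the primary non-inferiority analysis is in infection-naïve participants, the population of the Sample size section. Classify them by recorded history together with the anti-RBD result on the dose-1 serum. Report as supportive analyses all randomised participants, adjusted for infection status and with the arm-by-infection interaction, and the infected subgroup on its own. If the sponsor intends a mixed population instead, the Sample size section must be rewritten for it.

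The cost is mainly wording: Table 1 already has the dose-1 serum drawn from every participant, and Laboratory data assigns serum to the anti-RBD assay. The real price is power. The primary comparison has fewer participants, so power must be restated for the naïve set: with 50 per arm it is about 70% (one-sided 1.25%) or 79% (one-sided 2.5%). Within 75 per arm, the 69 naïve needed for 90% power at one-sided 2.5% are available only if at most 6 per arm were infected (75 − 69), and the 81 needed at one-sided 1.25% are out of reach. These figures include no allowance for dropout.
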